## Abstract

**Background:**

COVID-19 is associated with increased morbidity and mortality in patients with chronic kidney disease (CKD) stages G4-G5, on dialysis or after kidney transplantation (kidney replacement therapy, KRT). SARS-CoV-2 vaccine trials do not elucidate if SARS-CoV-2 vaccination is effective in these patients. Vaccination against other viruses is known to be less effective in kidney patients. Our objective is to assess the efficacy and safety of various types of SARS-CoV-2 vaccinations in patients with CKD stages G4-G5 or on KRT.

**Methods:**

In this national prospective observational cohort study we will follow patients with CKD stages G4-G5 or on KRT (*n* = 12,000) after SARS-CoV-2 vaccination according to the Dutch vaccination program. Blood will be drawn for antibody response measurements at day 28 and month 6 after completion of vaccination. Patient characteristics and outcomes will be extracted from registration data and questionnaires during 2 years of follow-up. Results will be compared with a control group of non-vaccinated patients. The level of antibody response to vaccination will be assessed in subgroups to predict protection against COVID-19 breakthrough infection.

**Results:**

The primary endpoint is efficacy of SARS-CoV-2 vaccination determined as the incidence of COVID-19 after vaccination. Secondary endpoints are the antibody based immune response at 28 days after vaccination, the durability of this response at 6 months after vaccination, mortality and (serious) adverse events.

**Conclusion:**

This study will fulfil the lack of knowledge on efficacy and safety of SARS-CoV-2 vaccination in patients with CKD stages G4-G5 or on KRT.

**Trial registration:**

The study protocol has been registered in clinicaltrials.gov(NCT04841785).

**Current knowledge about this subject**
COVID-19 has devastating impact on patients with CKD stages G4-G5, on dialysis or after kidney transplantation.Effective SARS-CoV-2 vaccination is very important in these vulnerable patient groups.Recent studies on vaccination in these patient groups are small short-term studies with surrogate endpoints.

**Contribution of this study**
Assessment of incidence and course of COVID-19 after various types of SARS-CoV-2 vaccination during a two-year follow-up period in not only patients on dialysis or kidney transplant recipients, but also in patients with CKD stages G4-G5.Quantitative analysis of antibody response after SARS-CoV-2 vaccination and its relationship with incidence and course of COVID-19 in patients with CKD stages G4-G5, on dialysis or after kidney transplantation compared with a control group.Monitoring of (serious) adverse events and development of anti-HLA antibodies.

**Impact on practice or policy**
Publication of the study design contributes to harmonization of SARS-CoV-2 vaccine studymethodology in kidney patients at high-risk for severe COVID-19.Data on efficacy of SARS-CoV-2 vaccination in patients with CKD will provide guidance for future vaccination policy.

**Supplementary Information:**

The online version contains supplementary material available at 10.1186/s12882-022-02680-3.

## Background

The coronavirus disease 2019 (COVID-19) pandemic has great impact on all aspects of society and healthcare. Patients with a severely impaired kidney function (CKD stages G4-G5) and patients on dialysis or after kidney transplantation, referred to as kidney replacement therapy (KRT), were shown to be extremely vulnerable. The COVID-19 associated mortality risk in these patient groups was reported to be 3- to 4-fold increased as compared to the general healthy population [1], which is considerably higher than the 1.5-to-2-fold increase that was described in patients with obesity, hypertension or diabetes [2]. Data from the European Renal Association – European Dialysis and Transplant Association (ERA-EDTA) COVID-19 database (ERACODA) show a high case fatality rate in patients on KRT [3, 4]. Therefore, the availability of an effective and safe vaccine will be extremely important for patients with CKD stages G4-G5 or on KRT.

Recently, efficacy and safety of different SARS-CoV-2 vaccine types have been demonstrated to be high in the general population [5–8]. So far, patients with CKD stages G4-G5 or on KRT were not or in low numbers included in these trials [9]. It is well known that vaccination efficacy against other viruses such as hepatitis B and influenza is considerably lower in patients with severely impaired kidney function, due to the immunosuppressive effect of uremic waste products [10]. A lesser antibody response after vaccination is to be expected in kidney transplant recipients due to the use of immunosuppressive agents. A recent Call to Action by the ERA-EDTA Council and ERACODA Working Group included the advice to perform dedicated vaccination studies to address this important knowledge gap regarding the efficacy of SARS-CoV-2 vaccination [11]. Recent studies have demonstrated the humoral response following SARS-CoV-2 vaccination in patients on KRT. One study showed a robust humoral response in the majority of haemodialysis patients after SARS-CoV-2 vaccination [12], but in a different study when compared to a control group, antibody titres were significantly lower [13]. Another study demonstrated a significantly reduced antibody response in 34 solid organ transplantation patients compared to health care workers [14]. Current data on SARS-CoV-2 vaccination efficacy in kidney patients report on surrogate endpoints, such as antibody titres. Clinical endpoints are currently lacking in the assessment of the efficacy of SARS-CoV-2 vaccination in kidney patients.

Therefore, we established the RECOVAC consortium (**RE**nal patients **CO**vid-19 **VAC**cination) in the Netherlands with active participation of the Dutch Kidney Patients Association (NVN). This consortium will perform the **L**ong-term **E**fficacy and **S**afety of **S**ARS-**CoV-2** vaccination (LESS CoV-2) study. In this study we aim to assess efficacy of SARS-CoV-2 vaccination in patients with CKD stages G4-G5 and on KRT in comparison to non-vaccinated control groups in a large-scale national registry study. We hypothesize that kidney patients obtain lesser protection from SARS-CoV-2 vaccination.

## Methods and analysis

### Study design

This is a prospective national observational cohort study which includes all kidney patients who were vaccinated against SARS-CoV-2 in the Dutch vaccination programme. Currently available vaccines in the Netherlands are the mRNA-1273 (Moderna), BNT162b2-mRNA (Pfizer), ChAdOx1 nCoV-19 (AstraZeneca) and Ad26.COV2.S (Janssen) vaccines [5–8]. Patients with CKD stages G4-G5 or on KRT received prioritization as medical high-risk group and predominantly received the mRNA-1273 vaccine in the Dutch vaccination programme. To assess the antibody dependent immune response after vaccination, blood samples will be collected at 28 days and at 6 months after the second vaccination with a home-based finger prick test. Antibody measurement will include both the receptor binding domain (RBD) of the spike (S) antigen and the nucleocapsid (N) antigen [15]. Combining these antibody measurements allows to distinguish a natural infection from an antibody response after S1-based vaccination.

Questionnaires will be obtained during a two-year follow-up period to assess the incidence of COVID-19 or (serious) adverse events ((S)AEs) after vaccination. The study events are demonstrated in Fig. 1. The questionnaires are shown in the supplemental materials.

**Fig. 1 Fig1:**
[figure not shown]
Study activities. “t = -1” = 1st vaccination, “t = 0” = 2nd vaccination, d = days, m = months*.* Details on the course of COVID-19 after vaccination will be collected from ERACODA which collects individual patient level data of adults on dialysis or with a functioning kidney allograft who are diagnosed with COVID-19

### Setting

The study starts in April 2021 amidst the COVID-19 pandemic when the Dutch vaccination program has started to vaccinate high-risk patients, including patients with kidney disease. COVID-19 incidence rates are still high and the health care system has not yet regained full capacity to exert routine care to all patients, due to lack of capacity.

### Study participants

The study population includes a subset of patients with CKD stages G4-G5 and patients on KRT in the Netherlands. The inclusion and exclusion criteria are mentioned in Table 1. Of note, patients will be eligible whether they have a history of COVID-19 or not.

**Table 1 Tab1:** Inclusion and exclusion criteria

*Inclusion criteria*	
1. Age of 18-80 years 2. Capable of understanding the purpose and risks of the study, to be fully informed and to give informed consent 3. Either - eGFR < 30 ml/min/1.73m^2^ but not on dialysis or with a kidney transplant - Haemodialysis or peritoneal dialysis - Kidney transplant recipient at least 6 weeks after transplantation	
*Exclusion criteria (≥ 1)*	
•Patients who opted out for the national dialysis (RENINE) and kidney transplantation (NOTR) registries.	

*eGFR* Estimated glomerular filtration rate

### Study enrolment

All patients who previously gave informed consent in two national registries, for dialysis patients (RENINE) and kidney transplant recipients (NOTR), are selected for enrolment. Patients with CKD stages G4-G5 will be enrolled from a cohort of non-university hospitals (Santeon). All patients eligible to the registry will be followed to assess incidence of COVID-19 after vaccination, (S)AEs and vaccination status. Data of non-vaccinated patients which will be derived from RENINE and NOTR registries serve as control. Furthermore, data on vaccination efficacy in the general population, which will be derived from the National Institute for Public Health and the Environment (RIVM), serve as a control group.

For measurement of antibodies after completion of SARS-CoV-2 vaccination we intend to include a random subset of patients with CKD stages G4-G5 (*n* = 4000), patients on dialysis (*n* = 4000), and patients after kidney transplantation (*n* = 4000) (Fig. 2). Patients older than 80 years are excluded from participation because they had priority in the Dutch national vaccination scheme over other high-risk groups. Consequently, they were vaccinated longer than 28 days ago, which is the accepted term in wherein finger-prick tests are obtained for antibody measurement.

**Fig. 2 Fig2:**
[figure not shown]
Study Enrolment Flowchart. HD = haemodialysis, PD = peritoneal dialysis, KTx = kidney transplantation, CKD = chronic kidney disease, Ab = antibody, (S)AEs = (serious) adverse events

### Informed consent for antibody measurement at home

All patients eligible to antibody measurement at home are offered two options to give informed consent, namely a written and a digital informed consent. We invited patients to register for the study by e-mail, mail and by distribution of flyers in all participating hospitals. Patients could apply for a patient information folder being sent to their home address or they could access the information folder at the website by scanning a QR-code. The QR-code directed the patients to a digital platform where they could give a digital informed consent, signed by entering a code sent to their mobile phone. In addition, we used our study website [16] to provide online access to the digital platform where informed consent could be given. This procedure enables rapid information provision of patients with minimal effort for local health care workers in the hospitals.

### Patient characteristics

The patient characteristics that will be obtained are listed in Table 2.

**Table 2 Tab2:** Patient baseline characteristics

*General*	
• Age • Sex • BMI	
*Renal disease*	
• Primary kidney disease • Dialysis modality • Type of kidney transplantation.	
*Laboratory parameters*	
• Serum creatinine (μmol/L), eGFR (ml/min1.73m^2^), except in dialysis patients • Urine creatinine (g/L), urine protein (g/L) or albumin (g/L), except in dialysis patients • HbA1c (mmol/mol)	
*Intoxications*	
• Smoking, alcohol	
*Comorbidity*	
• Coronary heart disease / PCI / CABG • Heart failure • Hypertension • Peripheral arterial disease and/or abdominal aortic aneurysm • Cerebrovascular accident • Dementia • Lung disease • Liver disease • Diabetes • Cancer • HIV	
*PROMs*	
• SF-12 and DSI in the subset of dialysis patients	
*Medication*	
• Antihypertensive drugs • Steroids or other immunosuppressive agents	
*COVID-19*	
• COVID-19 and severity before vaccination	

*BMI* Body Mass Index, *eGFR* estimated Glomerular Filtration Rate, *HbA1c* Haemoglobin A1c, *PCI* Percutaneous Coronary Intervention, *CABG* Coronary Arterial Bypass Grafting, *HIV* Human Immunodeficiency Virus, *PROMs* Patient Reported Outcome Measures, *SF-12* 12-item Short Form health survey, *DSI* Dialysis symptom index, *COVID-19* Coronavirus disease 2019

### Outcome definitions

For an overview of the clinical endpoints in this study we refer to Table 3.

**Table 3 Tab3:** Clinical endpoints LESS-CoV-2 study

*Primary endpoint*	
Incidence (per person-year) of COVID-19 in a two-years period after SARS-CoV-2 vaccination in patients with CKD stage G4-G5 or on KRT.	
*Secondary endpoints*	
Efficacy	
• The antibody based immune response to SARS-CoV-2 vaccination at 28 days after SARS-CoV-2 vaccination.	
• The durability of the antibody response at 6 months after SARS-CoV-2 vaccination	
Safety	
• Incidence of mortality	
• Incidence of AEs of specific interest as defined by (inter) national authorities	
• Incidence of a combined endpoint of acute rejection or graft failure in kidney transplant recipients	
• Incidence of HLA antibodies defined as cPRA > 5% in dialysis patients on the waiting list for their first kidney transplantation	
*Exploratory endpoints*	
Vaccination coverage rates	
Disease severity in patients who develop COVID-19, assessed as	
• Hospitalization	
• ICU admission	
• Mechanical ventilation	
PROMs in patients on dialysis	
SARS-CoV2 genotype in patients with COVID-19 (in case available)	

*COVID-19* Coronavirus Disease 2019, *SARS-CoV-2* Severe Acute Respiratory Syndrome Coronavirus-2, *CKD* Chronic Kidney Disease, *KRT* Kidney Replacement Therapy, *AEs* Adverse Events, *HLA* Human Leukocyte Antigen, *cPRA* Calculated Panel Reactive Antibody, *ICU* Intensive Care Unit, *PROMs* Patient Reported Outcome Measures

### Home based finger prick tests

Blood samples will be obtained through self-obtained sample collection by use of a home-based finger prick test. The finger prick tests will be sent by mail to all participants. Written instructions are given to apply the finger prick test and how to return the finger prick tests. This procedure enables blood sampling without further need of effort from local health care workers in the hospitals. Only hemodialysis patients were offered to contact their dialysis center, when they encounter difficulties during the blood sample collection.

### Antibody measurement

We will analyse the presence of antibodies against the RBD of the SARS-CoV-2 S-protein (IgG anti-RBD antibody) using the Sanquin anti-SARS-CoV-2 RBD IgG ELISA assay [15]. This is an indirect ELISA using microtiter plates coated with RBD and detection by monoclonal mouse anti-human IgG. The antibodies against the RBD are the primary constituent of the humoral immune response after SARS-CoV-2 vaccination. We combine this test with a Sanquin anti-SARS-CoV-2 nucleocapsid protein (NP) bridging ELISA. This test is an indirect ELISA using microtiter plates coated with NP and detection by biotin-labelled NP. Both antibodies against RBD and NP arise after a natural COVID-19 infection. In contrast, vaccination only induces antibodies to RBD, since NP is not part of any of the currently used vaccines. Combining these two tests enables us to differentiate between antibodies after vaccination or after previous COVID-19 infection.

### SARS-CoV-2 genotype variants

We intend to collect data on SARS-CoV-2 genotype variance in our study population if available from clinical practice. We aim to assess the efficacy of the various SARS-CoV-2 vaccine types used in our study population for protection against different SARS-CoV-2 strains.

### Statistical considerations

Baseline characteristics of vaccinated patients with CKD stages G4-G5 or on KRT will be compared with non-vaccinated patients with CKD stages G4-G5 or on KRT and the vaccinated general population using a two-sample t-test in case of continuous variables (or a Mann-Whitney U-test if data are not normally distributed), and a Pearson Chi-2 test in case of categorical variables.

#### Analysis of primary endpoint

Incidence rates of COVID-19 within 2 years after vaccination will be reported for each study population separately and incidence rates will be compared. Primary comparisons are comparisons of COVID-19 incidence rates in vaccinated patients versus non-vaccinated patients and versus the vaccinated general population. These comparisons will be made separately for patients with CKD stages G4-G5 or on KRT. For comparison of incidence rates, we will calculate crude hazard ratios. Vaccine efficacy will be reported as 100 × (1- hazard ratio). We will calculate model adjusted hazard ratios using multivariable Cox-regression, in case of imbalance in study populations regarding relevant characteristics, such as age, sex, comorbidity, kidney replacement modality and use of immunosuppressive agents. Cause specific hazard ratios will be estimated to account for competing risk of mortality. Starting date of follow-up will be the date of second vaccination in vaccinated patients. Starting date of follow-up in non-vaccinated patients will be the same date (or +/− 7 days from date of vaccination) as date of vaccination in the matched vaccinated patients to account for changes in incidence of COVID-19 over time. Non-vaccinated patients will be censored at the day of vaccination in case they are vaccinated before the end of follow-up. The aforementioned analyses will be repeated in patients with and patients without evidence of prior infection. Among vaccinated patients, incidence rates will also be compared across the various vaccines that will be used. For this purpose, vaccinated patients with CKD stages G4-G5 or on KRT and general population again will be analysed separately.

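### No planned primary analysis compares vaccine efficacy between kidney patients and the public; the vaccinated-versus-vaccinated contrast mixes efficacy with background risk, and 100 × (1 − HR) is not an efficacy there

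*Protocol article*

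**What the plan says.** All references are to the protocol article.

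- **Hypothesis (Background):** "We hypothesize that kidney patients obtain lesser protection from SARS-CoV-2 vaccination". The stated aim just before it is efficacy "in comparison to non-vaccinated control groups in a large-scale national registry study".
- **Primary comparisons (Analysis of primary endpoint):** "Primary comparisons are comparisons of COVID-19 incidence rates in vaccinated patients versus non-vaccinated patients and versus the vaccinated general population". They are to be made separately for CKD stages G4-G5 and for kidney replacement therapy.
- **Effect measure (same section):** "For comparison of incidence rates, we will calculate crude hazard ratios". The next sentence begins "Vaccine efficacy will be reported as 100 × (1- hazard ratio" and does not say which of the two comparisons it covers.
- **Adjustment (same section):** multivariable Cox regression if the groups are imbalanced on relevant characteristics, "such as age, sex, comorbidity, kidney replacement modality and use of immunosuppressive agents".
- **Data sources (Study enrolment):** non-vaccinated controls come from the dialysis registry (RENINE) and the transplant registry (NOTR). A further control is "data on vaccination efficacy in the general population, which will be derived from the National Institute for Public Health and the Environment (RIVM". CKD G4-G5 patients come from a group of non-university hospitals, and no non-vaccinated source is named for them.

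**The concern.** Protection by a vaccine is a within-population quantity: the hazard in vaccinated people relative to comparable non-vaccinated people. Lesser protection in kidney patients therefore means that this ratio lies closer to 1 in patients than in a reference population. The Background reports high efficacy in the general population, so that is the natural reference.

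The first primary contrast gives the quantity for patients. The second sets vaccinated patients against vaccinated members of the public. Neither sets one efficacy against the other. The second contrast is the only one involving the public, so readers will be drawn to take it as evidence on the hypothesis. Its value depends on how often each population meets the virus and is tested, as well as on the vaccine. A primary result could then suggest or conceal a deficit in protection for reasons unrelated to vaccination. If the efficacy formula is applied to it as well, the article would report as efficacy a number that is not one.

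**Working it through.** The article gives no event count, efficacy value, significance level or power for this comparison, so there is no figure to reproduce. The check is algebraic, and every numerical input below is an assumption.

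**Definitions.** Let b be the COVID-19 hazard in unvaccinated patients divided by that in the unvaccinated public. Let VEp and VEg be the true efficacies in patients and public.

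**Contrast 1** (vaccinated versus non-vaccinated patients): HR1 = 1 − VEp, so 100 × (1 − HR1) is an efficacy.

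**Contrast 2** (vaccinated patients versus vaccinated public): HR2 = b × (1 − VEp)/(1 − VEg).

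**What the hypothesis concerns:** RHR = (1 − VEp)/(1 − VEg). This is the vaccinated versus non-vaccinated HR in patients divided by the same HR in the public. It does not contain b.

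| b (assumed) | HR2, VEp = VEg | 100 × (1 − HR2) | HR2, VEp 70%, VEg 90% | 100 × (1 − HR2) |
|---|---|---|---|---|
| 0.5 | 0.5 | +50% | 1.5 | −50% |
| 0.75 | 0.75 | +25% | 2.25 | −125% |
| 1 | 1.0 | 0% | 3.0 | −200% |
| 1.5 | 1.5 | −50% | 4.5 | −350% |
| 2 | 2.0 | −100% | 6.0 | −500% |
| 3 | 3.0 | −200% | 9.0 | −800% |

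In every row RHR is 1.0 for equal efficacy and 3.0 for 70% versus 90%.

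**Results**

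1. With equal efficacy, HR2 = b, whether the common efficacy is 70% or 90%.
2. HR2 = 1.5 arises both from equal protection with b = 1.5 and from 70% versus 90% with b = 0.5. Solving VEp = 1 − HR2 × (1 − VEg)/b with HR2 = 1.5 and VEg = 90% gives VEp = 70%, 80%, 85%, 90%, 92.5% and 95% for b = 0.5, 0.75, 1, 1.5, 2 and 3. The same observed ratio is compatible with lower, equal or higher efficacy in patients.
3. Even at b = 1, where HR2 does equal RHR, 100 × (1 − HR2) is 0% under equal efficacy. It is not an efficacy.
4. Suppose 200 events, 1:1 allocation and two-sided 0.05 (all assumed). By the Schoenfeld approximation, the chance of a significant HR2 when efficacy is equal is Φ(√(200/4) × |ln b| − 1.96):
   - b = 0.75: Φ(7.07 × 0.288 − 1.96) = 53%
   - b = 1.5: Φ(7.07 × 0.405 − 1.96) = 82%
   - b = 2: Φ(7.07 × 0.693 − 1.96) = 99.8%

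**Does the planned adjustment remove b?** Not reliably. It is conditional on imbalance. Comorbidity is on the list and may absorb part of b, but nothing listed measures exposure, shielding or testing. Kidney replacement modality does not vary in the general population. The Background gives immunosuppressive agents as a reason to expect a weaker antibody response after transplantation, so adjusting for them could remove part of the effect under study. The rule that matches start dates to allow for changing incidence is written for non-vaccinated patients; none is stated for the general population.

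**The case against.** A fair defence has four parts.

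**The article never names contrast 2 as the test of the hypothesis.** This stands. The hypothesis sentence gives no comparator or scale, the aim points to non-vaccinated controls, and Table 3 defines the primary endpoint as incidence. As a comparison of breakthrough incidence, contrast 2 is legitimate. The gap is that no stated analysis compares efficacies, while a contrast that looks as if it might is made primary.

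**The ingredients are planned.** This also stands. A reader might infer that the hypothesis cannot be tested in this study. The documents do not support that: contrast 1 yields an efficacy in patients, and the RIVM data on efficacy in the public are a named control. A formal ratio might be set out in a fuller plan that is not shown. However, the article itself fixes the primary comparisons and the formula, and these are what need correcting.

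**The adjustment goes beyond age and sex.** Correct. A reader might infer age-and-sex adjustment only, but that belongs to the antibody sensitivity analyses. The primary Cox model also lists comorbidity, modality and immunosuppression. The objection to contrast 2 therefore rests on exposure, shielding, testing and calendar alignment.

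**The formula was probably meant only for contrast 1.** This is plausible, since efficacy ordinarily implies an unvaccinated comparator. The article does not say that efficacy will be calculated between two vaccinated groups, and it should not be read as a declared intention. The wording covers both contrasts, and one clause would settle it.

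The numerical range is also open to challenge, because nothing in the article fixes b. A complete masking of a 70% versus 90% difference (HR2 = 1.0) needs b = 1/3; for b from 0.5 to 3, HR2 is never below 1.5.

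**Conclusion.** The concern holds in this limited form. The hypothesis of lesser protection is testable from data the study plans to obtain, but no analysis under Analysis of primary endpoint tests it. The vaccinated-versus-vaccinated comparison cannot do so alone, because it multiplies the ratio of interest by an unknown background risk ratio. As worded, the efficacy formula extends to that comparison, where it has no meaning as efficacy.

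The identity HR2 = b × RHR, with b and efficacy expressed as hazard ratios, needs no numerical input. The sizes do: the +50% to −200% range under equal efficacy rests on assumed b of 0.5 to 3, and the false-signal probabilities also rest on the assumed events, allocation and significance level. They illustrate sensitivity and do not predict what the study will find.

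It would also go too far to conclude that a ratio of hazard ratios solves everything. It removes b but keeps any difference between the populations in how vaccinated and non-vaccinated people are selected. Study design notes that these patients were prioritised for vaccination, so those who stayed unvaccinated may be a selected group.

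**What to change.** 1. **Limit the formula.** State that 100 × (1 − HR) applies only to vaccinated versus non-vaccinated comparisons.
2. **Name the test of the hypothesis.** Compare the patient vaccinated versus non-vaccinated HR with the general-population HR implied by the RIVM efficacy (HR = 1 − VE/100). Estimate ln HR(patients) − ln HR(public), with variance SE²(patients) + SE²(public), treating the two estimates as independent. Take the public SE from the RIVM 95% confidence interval as (ln upper − ln lower)/(2 × 1.96) on the HR scale. Exponentiate to report the ratio of hazard ratios with its interval. If RIVM supplies individual data, a vaccination-by-population interaction does the same job.
3. **Align the two sources** on age, calendar period, case definition and vaccine.
4. **Set the scope.** Do this for dialysis and transplant patients. Include CKD G4-G5 only if a non-vaccinated control source is identified, since Study enrolment names only RENINE and NOTR.
5. **Relabel contrast 2** as a descriptive relative breakthrough incidence.

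**Cost.** Items 1 and 5 are wording. Items 2 and 3 use data already planned, provided RIVM gives an interval and enough detail to align the sources. A control source for CKD G4-G5 would be additional work. The interval will be wider: with d events per group, the approximate variance of ln HR2 has two terms of the form 1/d, while that of ln RHR has four, because both non-vaccinated groups enter. The assumption of similar confounding in the two populations should be stated with the result.

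### Vaccine efficacy is read from a vaccinated versus non-vaccinated contrast adjusted only for measured covariates, and recorded deaths are not used to check for health selection

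*Protocol article*

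**What the plan says.** All references are to the protocol article; no separate analysis plan is shown.

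- **Contrast.** Analysis of primary endpoint: "Primary comparisons are comparisons of COVID-19 incidence rates in vaccinated patients versus non-vaccinated patients and versus the vaccinated general population". Efficacy is defined there as 100 × (1 − hazard ratio). This point concerns the first comparison, with non-vaccinated patients.
- **Estimate.** "For comparison of incidence rates, we will calculate crude hazard ratios". Adjustment is conditional: "We will calculate model adjusted hazard ratios using multivariable Cox-regression, in case of imbalance in study populations regarding relevant characteristics", with examples "such as age, sex, comorbidity, kidney replacement modality and use of immunosuppressive agents".
- **Time alignment.** Vaccinated patients start follow-up at the second vaccination. Controls start within 7 days of the same date "as date of vaccination in the matched vaccinated patients to account for changes in incidence of COVID-19 over time", and are censored if they are vaccinated later. No matching on health status is stated.
- **Who is compared.** Study design: "Patients with CKD stages G4-G5 or on KRT received prioritization as medical high-risk group". Under Study enrolment, non-vaccinated controls come from the dialysis and transplant registries. Their number is not given; vaccination coverage is an exploratory endpoint in Table 3.
- **Deaths.** Table 3 lists "Incidence of mortality" under safety, and the Safety section compares it with methods similar to the primary analysis. The primary analysis treats death as a competing risk through cause-specific hazards. Neither use is linked back to efficacy.
- **Limitations.** The Discussion names the level of viral spread, the vaccine mix and the restriction to humoral response. It does not name selection into vaccination.

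**The concern.** Three features make health selection plausible. The group was prioritised, so controls are registry patients not yet vaccinated while vaccination was being offered to them. A vaccinated patient must have survived, and been well enough, to receive two vaccinations before follow-up starts; a control need only be alive and under observation on the matched date. Controls who are vaccinated later leave the comparison, so the unvaccinated person-time narrows over two years.

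Calendar alignment removes differences in epidemic intensity but not differences in health. Covariate adjustment removes only what is measured. Table 2 lists comorbidities but no frailty or functional measure, apart from SF-12 and DSI in a dialysis subset, which are not named for adjustment.

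At stake is the meaning of the headline result. A hazard ratio below 1 for COVID-19 would be reported as efficacy, and a low hazard ratio for death as safety, although both could come partly from who was vaccinated. In the safety comparison, the same selection could also mask harm.

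**Working it through.** **No figure to reproduce.** The article states no event rate, assumed efficacy or power calculation for this contrast; 12,000 is 3 × 4,000, the intended antibody subset. Every prevalence, risk ratio, mortality rate and unvaccinated share below is an assumption.

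**1. Effect on efficacy.** Let an unmeasured binary factor have prevalence pv in the vaccinated and pu in the unvaccinated, and multiply COVID-19 risk by RR. The bias factor is B = [1 + pv(RR − 1)] / [1 + pu(RR − 1)], and the apparent HR is the true HR × B. With pv = 0.20:

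| pu | RR | B | Apparent efficacy, true 0% | Apparent efficacy, true 50% |
|---|---|---|---|---|
| 0.30 | 1.5 | 1.10/1.15 = 0.957 | 4% | 52% |
| 0.40 | 2 | 1.20/1.40 = 0.857 | 14% | 57% |
| 0.50 | 3 | 1.40/2.00 = 0.700 | 30% | 65% |

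The size of the control group does not enter B; only the difference in prevalence does.

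**2. What the same selection does to death without COVID-19.** The same formula with assumed death risk ratios of 2, 3 and 4 gives 1.2/1.3 = 0.92, 1.4/1.8 = 0.78 and 1.6/2.5 = 0.64. The death hazard ratio does not convert into a bias in efficacy: if the factor raised death but not infection (RR = 1 for COVID-19), B would be 1 and efficacy unbiased.

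**3. Why follow-up should be split.** Suppose a share f of the unvaccinated, and none of the vaccinated, are near the end of life with R times the usual death rate. At the start of follow-up the hazard ratio with no vaccine effect is 1/(1 − f + fR):

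| f | R = 5 | R = 10 |
|---|---|---|
| 2% | 0.93 | 0.85 |
| 5% | 0.83 | 0.69 |
| 10% | 0.71 | 0.53 |

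These ratios move towards 1 as high-risk patients die. For f = 5%, R = 10 and a base rate of 0.10 per year over two years, per control:

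- deaths = 0.95(1 − e^−0.2) + 0.05(1 − e^−2) = 0.172 + 0.043 = 0.215
- person-years = 0.95(1 − e^−0.2)/0.1 + 0.05(1 − e^−2)/1.0 = 1.722 + 0.043 = 1.765
- rate = 0.215/1.765 = 0.122, so the rate ratio is 0.10/0.122 = 0.82, against 0.69 at the start.

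Likewise f = 10%, R = 10 gives 0.69 instead of 0.53, and f = 5%, R = 5 gives 0.88 instead of 0.83. Selection of this kind shows most clearly early.

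**4. Can the check see it?** Power = Φ(√[d·s(1 − s)] × |ln HR| − 1.96), with d deaths and unvaccinated share s. Assume n = 8,000 on dialysis or transplanted (2 × 4,000, a stand-in because the registry cohort size is not stated), one year of follow-up and 10% yearly non-COVID mortality in the vaccinated. For s = 3% and HR 0.5, d = 8,000 × (0.97 × 0.10 + 0.03 × 0.20) = 824, so √(824 × 0.0291) × 0.693 − 1.96 = 1.43 and power is 0.92.

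| n | HR | s = 3% | s = 5% | s = 10% |
|---|---|---|---|---|
| 8,000 | 0.5 | 0.92 | 0.99 | >0.99 |
| 8,000 | 0.7 | 0.41 | 0.60 | 0.87 |
| 4,000 | 0.5 | 0.67 | 0.87 | 0.99 |
| 4,000 | 0.7 | 0.23 | 0.35 | 0.59 |

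Strong selection would usually be visible. Moderate selection could be missed if few are unvaccinated.

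**The case against.** The strongest reply is that a journal article may leave sensitivity analyses to an unseen full document, and that nothing in the primary analysis section is false. That has weight for fine detail. Here, though, the article itself sets out the confounding control for its primary contrast, fixes two uses of the deaths and lists its limitations without this threat.

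Other objections stand and limit the point:

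- A reader might infer that the controls are a small remainder of refusers and patients too ill to be vaccinated. The article does not say so. Vaccination was still being rolled out, so controls include patients not yet vaccinated. Their number, make-up and the direction of selection are inferences.
- A reader might infer that adjustment is confined to five characteristics. The list is given as examples, and Table 2 includes dementia, cancer, heart failure and other partial proxies for frailty.
- A reader might infer that nothing planned could show selection. The planned mortality comparison might show it incidentally; what is missing is its use for interpreting efficacy.
- A reader might infer that a death hazard ratio excluding 1 proves efficacy to be confounded. It does not: a factor may affect death but not infection, and a true vaccine effect on death would also move the ratio.

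**Conclusion.** The point holds in a limited form and is worth acting on. The primary contrast with non-vaccinated patients relies on date alignment and conditional adjustment for measured covariates, reports the result as vaccine efficacy, and does not use deaths without COVID-19 to judge residual health selection. The consequence is one of interpretation: selection could pass as efficacy or as safety.

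The size is unknown. The assumed scenarios range from trivial (50% read as 52%) to material (a vaccine with no effect read as 30%). They rest on invented prevalences and risks, and the start-of-follow-up death ratios overstate what two full years would show. The documents do not support a statement that efficacy will be biased, in which direction, or by how much.

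**What to change.** From the same date-matched, cause-specific Cox model, crude and adjusted, report the hazard ratio with confidence interval for death without preceding COVID-19 as a negative-control outcome beside vaccine efficacy. Split it into early and later follow-up at a cut-point fixed in advance. Interpret both efficacy and the mortality safety comparison in its light, and name selection into vaccination among the limitations.

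State the reading rule in advance. A hazard ratio clearly below 1, especially early, is evidence of residual health selection, and efficacy is reported with that caution. It does not trigger an automatic declaration that efficacy is confounded, or a bias-corrected figure. A null result with a wide interval is not reassurance.

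The cost is small, because the planned competing-risk framework already treats death before COVID-19 as an event and no new data are needed. The downsides should be stated: undiagnosed COVID-19 deaths may be misclassified; a true vaccine effect on death cannot be fully separated from selection; power is limited for moderate selection if few are unvaccinated; and the check does not address differences in testing or exposure behaviour.
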